## Abstract

**Background:**

‘Home-grown’ school feeding programmes are complex interventions with the potential to link the increased demand for school feeding goods and services to community-based stakeholders, including smallholder farmers and women’s groups. There is limited rigorous evidence, however, that this is the case in practice. This evaluation will examine explicitly, and from a holistic perspective, the simultaneous impact of a national school meals programme on micronutrient status, alongside outcomes in nutrition, education and agriculture domains.

The 3-year study involves a cluster-randomised control trial designed around the scale-up of the national school feeding programme, including 116 primary schools in 58 districts in Ghana. The randomly assigned interventions are: 1) a school feeding programme group, including schools and communities where the standard government programme is implemented; 2) ‘home-grown’ school feeding, including schools and communities where the standard programme is implemented alongside an innovative pilot project aimed at enhancing nutrition and agriculture; and 3) a control group, including schools and households from communities where the intervention will be delayed by at least 3 years, preferably without informing schools and households. Primary outcomes include child health and nutritional status, school participation and learning, and smallholder farmer income. Intermediate outcomes along the agriculture and nutrition pathways will also be measured. The evaluation will follow a mixed-method approach, including child-, household-, school- and community-level surveys as well as focus group discussions with project stakeholders. The baseline survey was completed in August 2013 and the endline survey is planned for November 2015.

**Results:**

The tests of balance show significant differences in the means of a number of outcome and control variables across the intervention groups. Important differences across groups include marketed surplus, livestock income, per capita food consumption and intake, school attendance, and anthropometric status in the 2–5 and 5–15 years age groups. In addition, approximately 19 % of children in the target age group received some form of free school meals at baseline.

**Conclusion:**

Designing and implementing the evaluation of complex interventions is in itself a complex undertaking, involving a multi-disciplinary research team working in close collaboration with programme- and policy-level stakeholders. Managing the complexity from an analytical and operational perspective is an important challenge. The analysis of the baseline data indicates that the random allocation process did not achieve statistically comparable treatment groups. Differences in outcomes and control variables across groups will be controlled for when estimating treatment effects.

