The GSFP selected 58 districts in which the programme will be implemented. In each of these districts, two candidate schools were selected and each school was randomly assigned to the treatment or to the control. A protocol was designed in order to ensure that the schools were comparable based on data from the Education Management Information system (EMIS) and that contamination between the two schools in each district will be minimised. This will allow comparison of outcomes of the intervention against the control group at the school level in 58 districts. The 58 schools assigned to the intervention were then randomly assigned to regular GSFP and HGSF+. In this way the randomisation of the HGSF+ intervention occurs at the district level. The number of 58 schools is based on power calculations (see Appendix 1) determined with the objective of achieving statistical validity and representativeness for the main outcomes of interest.

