### Anaemia sub-study

The impact evaluation includes a sub-study focussing on nutrition in school feeding with and without micronutrient fortification. A sub-group of 14 of the 29 HGSF+ groups was randomly assigned to receive food fortification (the HGSF++ group) in addition to training and sensitisation activities that are part of the HGSF+ pilot (see Fig. 3). Data will be collected from children aged 5–15 years in the HGSF++, HGSF+, GSFP and control communities. Targeted schools were surveyed as part of the broader impact evaluation baseline.

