### Methods of analysis

The randomised design allows for the identification of causal impacts of interventions using comparisons of mean outcomes between the randomised treatment arms at endline. The analysis will follow the intention-to-treat approach as protocol and as treated, using econometric analysis for all the relevant outcomes of the intervention. Following Bruhn and McKenzie, impact will be assessed for the different treatment arms using both a ‘difference-in-difference’ (DID) estimator and a single difference analysis of covariance (ANCOVA) model [14].

The DID estimate is calculated as the average change in the outcome of interest (*Y*) in the treatment arm (*T*) minus the change in outcome in the control group (*C*), or:$$ {\Delta}^{DID}=E\left[\left({\overline{Y}}_1^T-{\overline{Y}}_0^T\right)-\left({\overline{Y}}_1^C-{\overline{Y}}_0^C\right)\right]. $$

A difficulty of DID analysis is serial correlation [15] resulting from unobserved factors affecting the outcomes that are themselves correlated over time and that produce auto-correlated errors and invalid standard errors. Serial correlation affects estimated standard errors and can lead to erroneous acceptance or rejection of null hypotheses but not the estimation of the effect size of the intervention. Thus, it may lead to erroneously finding or not finding a statistically significant impact of the intervention. Angrist and Pischke illustrate how this problem can be addressed by calculating clustered standard errors [16], a procedure that is easily implemented using Stata software. Clustered standard errors will also be employed in all cases in which correlated outcomes are observed within the same unit of analysis. For example, when the impact of the intervention is analysed at the school level and test scores within school are obviously correlated. Similarly, clustered standard error will be used at the household level when the project is affecting more than one child within the same family, as in the case of impact on younger siblings.

The single difference model specification has the following form:$$ {Y}_{i1}={\beta}_0+{\beta}_1{T}_i+{\beta}_2{Y}_{i0}+{\varepsilon}_i, $$

where *Y*_*i*0_ is the outcome variable at baseline, *Y*_*i*1_ is the outcome variable at endline and *T*_*i*_ is a dummy variable for the treatment. The ANCOVA estimator has been shown to provide a more efficient estimate of programme impact when auto-correlation of outcomes is low [14].

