Household expenditure on education	2626	214 [333]	1163	204 [328]	722	195 [311]	375	233 [340]	366	260 [374]	0.1926	0.0034	0.3013
Household expenditure on transport	2626	317 [415]	1163	315 [407]	722	297 [393]	375	352 [447]	366	326 [447]	0.8157	0.0607	0.4316
% share of HH expenditure spent on food	2626	59.8 [15.8]	1163	59.6 [16.4]	722	60.3 [15.4]	375	58.0 [14.0]	366	61.1 [16.0]	0.5613	0.3073	0.0049

Estimates are expressed as mean and standard deviation

*BMI* body mass index, *HH* household. * T-test statistics for comparisons across treatment arms

In the education domain, 92 % of children aged 5–15 years were enrolled in school, and mean enrolment rates were marginally lower in the control population (0.91, SD 0.29) compared to the school feeding group (0.93, SD 0.26). Significant differences were also found for age of first enrolment, the number of times that a year was repeated, and across all the four test scores.

In the nutrition domain for children aged 5–15 years, the mean z-scores for the anthropometrics measures of height for age and BMI for age were −0.925 (SD 1.35) and −0.592 (SD 0.924) respectively, with significant differences across the GSFP versus HGSF comparison groups. Iron status, as measured through haemoglobin levels, for the sub-sample of children (*n* = 714) who were assessed, was on average 11.3 g/dL (SD 1.34), just below the 11.5 g/dL cut-off for non-anaemia in the 5–11 years age group.

In terms of household socio-economic characteristics, there were neither significant differences among the treatment groups for the mean education levels of mothers and household heads, nor for household size. There was, however, a significant difference in terms of per-capita household expenditure quintiles between households in the GSFP and HGSF groups, but no other substantive differences with regards to household expenditure were observed.

In the agriculture domain, across the survey population the mean production of maize over the previous 12 months was 787 kg (SD 1751), with average household sales of maize during the same period of 393 kg (SD 1196). Mean household production of rice was 141 kg (SD 625), with average annual sale volumes of 84 kg (SD 484). Significant differences were found across treatment arms in terms of maize production and sales.

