In addition, approximately 19 % of children in the target age group (5–15 years) received some form of free school meals at baseline. Similar findings were reported in a similar study in Mali in 2013 by Masset and Gelli [13] where, because of information flow constraints, the original list of schools used in the randomisation included schools with school feeding. This finding has important implications in terms of the evaluation design, considerably reducing sample sizes available for comparisons after the follow-up survey. The small sample sizes between the HGSF+ and HGSF++ comparisons are a particular concern, and power calculations using the baseline data suggest folding these two arms into one, adding micronutrient sprinkles to the HGSF+ intervention.

Significant differences were found in the means of a number of outcome and control variables across the intervention groups. It appears, therefore, that at baseline the random allocation process did not achieve statistically comparable treatment groups. In particular, important differences across groups include marketed surplus, livestock income, per capita food consumption and intake, school attendance, anthropometric status in the 2–5 and 5–15 years age groups. Differences in outcome and control variables across groups will be controlled when estimating treatment effects. More in-depth analyses of the very rich baseline dataset, examining the associations between key outcomes and variables along the complex agriculture-nutrition are also underway.

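### The Table 6 balance tests ignore the clusters that were randomised, so they do not support the statement that allocation failed to give statistically comparable groups.

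*Protocol article*

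**What the plan says.** Design. The trial is described as "including 116 primary schools in 58 districts in Ghana". Under Random assignment and manipulation of treatments: "In each of these districts, two candidate schools were selected and each school was randomly assigned to the treatment or to the control". For regular GSFP against HGSF+: "In this way the randomisation of the HGSF+ intervention occurs at the district level". Under Anaemia sub-study: "A sub-group of 14 of the 29 HGSF+ groups was randomly assigned to receive food fortification". The three randomised contrasts therefore have 58 vs 58 schools in district pairs, 29 vs 29 districts, and 15 vs 14 clusters.

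Analysis. Methods of analysis provides for clustered standard errors wherever outcomes correlate within a unit, and gives as an example that "test scores within school are obviously correlated". Both planned estimators use the baseline outcome: difference-in-difference by subtraction, ANCOVA as a covariate.

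Baseline. The Table 6 footnote describes its p-values only as "T-test statistics for comparisons across treatment arms". The Abstract concludes: "The analysis of the baseline data indicates that the random allocation process did not achieve statistically comparable treatment groups". The Discussion repeats this and adds: "Differences in outcome and control variables across groups will be controlled when estimating treatment effects". The Results and Discussion also call the differences small, and the Discussion says such differences can arise from sampling error.

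**The concern.** A t-test that counts about 6,000 children or 2,626 households as independent, when 116, 58 or 29 clusters were randomised, understates the standard error and gives p-values that are too small. If Table 6 was computed that way, its significant results are not sound evidence about the allocation.

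Two things are at stake. The Abstract carries a conclusion against the trial's own allocation that readers will take at face value. And control for baseline differences is tied to the differences found, so the choice of covariates beyond the baseline outcome could follow invalid tests instead of prognostic value.

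**Working it through.** **1. Reproduce the printed p-values.** Inputs: n, mean and SD from Table 6, pooling GSFP, HGSF+ and HGSF++ into school feeding (SF), and HGSF+ and HGSF++ into HGSF. Formula: t = difference / (s × √(1/n₁ + 1/n₂)), with s the pooled SD and n₁ + n₂ − 2 degrees of freedom.

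Example, height-for-age, GSFP vs HGSF: HGSF mean = (730 × −0.888 + 705 × −0.827)/1435 = −0.858; difference −0.105; s = 1.283; t = −0.105 / (1.283 × √(1/1494 + 1/1435)) = −2.21; p = 0.0269.

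| Comparison | Computed p | Printed p |
|---|---|---|
| Height-for-age, GSFP vs HGSF | 0.0269 | 0.0268 |
| Maize production, SF vs control | 0.0435 | 0.0439 |
| Maize production, GSFP vs HGSF | 0.0374 | 0.0376 |
| Maize sales, GSFP vs HGSF | 0.0054 | 0.0057 |
| Maths, GSFP vs HGSF | 0.0044 | 0.004 |
| Raven's, HGSF+ vs HGSF++ | 0.0019 | 0.002 |

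No clustering was used. A few rows (for example enrolment and free school meals) reproduce only roughly, because of rounded means or apparent misprints.

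**2. Allow for clustering.** Design effect DE = 1 + (m − 1) × ICC, with m = observations per cluster. The corrected statistic is t/√DE, on clusters − 2 degrees of freedom.

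ICCs from Appendix 1: Raven's 0.14; height-for-age 0.08. Maths and maize have no stated ICC, so 0.05 to 0.14 is my assumption.

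- Height-for-age, GSFP vs HGSF: m = 2929/58 = 50.5; DE = 1 + 49.5 × 0.08 = 4.96; t = 2.21/2.23 = 0.99; p = 0.32.
- Raven's, HGSF+ vs HGSF++: m = 1590/29 = 54.8; DE = 1 + 53.8 × 0.14 = 8.54; t = 3.11/2.92 = 1.07; p = 0.30.
- Maths, GSFP vs HGSF: m = 3238/58 = 55.8; DE 3.74 to 8.68; p = 0.15 to 0.34.
- Maize sales, GSFP vs HGSF: m = 1463/58 = 25.2; DE 2.21 to 4.39; p = 0.07 to 0.19.
- Maize production, SF vs control, unpaired: m = 2626/116 = 22.6; DE 2.08 to 4.03; p = 0.16 to 0.32.

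**3. How often such a test rejects by chance.** The rate for a nominal 5% test is 2 × (1 − Φ(1.96/√DE)). At about 50 children per cluster it is about 38% at ICC 0.08 (DE 4.94) and 49% at ICC 0.14 (DE 7.9).

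**4. What survives.** Table 6 has 31 rows × 3 comparisons = 93 p-values, of which 30 are printed below 0.05. Applying one common ICC to all of them, unpaired, the number still below 0.05 is about 17 at ICC 0.02, 12 at 0.05, 6 at 0.08 and 3 at 0.14. Valid tests under chance alone would give about 0.05 × 93 ≈ 5 on average. The three left at 0.14 are all SF vs control: literacy (0.04), digit span (0.03) and child education expenditure (0.002).

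**5. Pairing, for SF vs control only.** If the school effects within a district pair have correlation r, DE becomes 1 + (m − 1) × ICC − r × m × ICC, on 57 degrees of freedom. No r is given, so 0.3 to 0.5 is assumed. For maths (t = 5.04, m = 50.2, ICC 0.14), DE falls from 7.89 to 5.78 or 4.38, and p from 0.08 to about 0.04 or 0.02. For Raven's, p falls from 0.22 to about 0.15 or 0.10.

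**The case against.** The strongest reply is that this is a descriptive table. The impact analysis is committed to clustered standard errors, with multilevel models as a check, and both estimators take in the baseline outcome whatever Table 6 shows. That stands, and it lowers the severity.

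The corrected p-values also depend on borrowed ICCs. The Raven's figure comes from a 36-item test in a 2003 sample, and the height-for-age figure from under-5 data. They are rough guides. At ICC 0.05 maths SF vs control is still 0.008 before any pairing, so some imbalance may be real in the clustered sense. This also stands.

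Three stronger readings are tempting.

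- *Every baseline difference is an artefact.* The survivors above contradict that. Livestock income, per-capita food consumption and intake, and 2–5-year anthropometry, which the Abstract and Discussion also name, are not in Table 6 and cannot be checked.
- *The article says randomisation was broken.* It says the groups were not statistically comparable, and itself points to sampling error; it does not allege a faulty procedure.
- *Balance p-values formally select the covariates.* The text ties control to the differences that exist, but states no threshold, algorithm or covariate list.

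What the reply does not remove is that the p-values are wrong for the design and that the Abstract draws its conclusion from them. Pairing does not help the GSFP vs HGSF or HGSF+ vs HGSF++ contrasts.

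**Conclusion.** The point holds in limited form. That Table 6 was computed without clustering follows from the printed figures and needs no assumption. That its p-values are too small follows from the cluster allocation and the article's own ICCs; how much too small depends on ICCs known only approximately. On those guides, the flagged differences in height-for-age (GSFP vs HGSF) and Raven's (HGSF+ vs HGSF++) are well within chance. So, over the assumed ICC range, are maths and maize sales (GSFP vs HGSF) and, unpaired, maize production (SF vs control). For SF vs control, literacy, digit span, child education expenditure and probably maths may stay significant once pairs are used.

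The statement about non-comparable groups is therefore unsupported by Table 6 as analysed, though not shown to be false for every variable. The harm is confined to that published conclusion and to the choice of additional covariates. Should-fix.

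**What to change.** 1. Recompute the three p-value columns of Table 6 with errors clustered at the randomised unit: school with district-pair effects for SF vs control, district for GSFP vs HGSF, cluster for HGSF+ vs HGSF++. Add standardised differences, and do the same for the named variables not shown in the table.
2. Reword the Abstract and Discussion to report chance imbalance in named variables. Keep the wording on non-comparability only where the clustered results support it.
3. Leave the baseline-outcome adjustment in both estimators as it is. For additional covariates, replace control for whichever differences exist with a set fixed before endline analysis on design and prognostic grounds: district pair or region, farmer stratum, age, sex, and the variables used for matching and for balancing the district allocation. Do not choose them by baseline significance.

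Cost: re-running one table, rewording a few sentences and fixing a covariate list. No new data are needed.

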**Trial registration number:**

ISRCTN66918874 (registered on 5 March 2015).

## Background

School feeding programmes have been a key response to the recent food and economic crises and function to some degree in nearly every country in the world [1]. School feeding is a multi-sectoral intervention with effects across education, health and nutrition, and with the potential for benefits across a life course. Rigorous studies have shown that school feeding programmes can improve school attendance and learning, as well as a child’s physical and psycho-social health (see [2] for a recent review). These effects are heterogeneous and context-specific, depending also on the quality of programme implementation. There is no rigorous evidence on the impact of providing a reliable market for smallholder farmers through ‘home-grown’ school feeding (HGSF) approaches [1, 2]. In HGSF, the demand for food and services from school feeding is channelled explicitly to smallholder farmers and other stakeholders involved in the school feeding supply chain. As most of the studies in the scientific literature in low-income settings involve humanitarian aid, there is also a paucity of evidence on government-led programmes operating at scale in low- and middle-income countries [1]. This study is aimed at addressing these research gaps by evaluating the full cost and impacts of alternative school feeding implementation approaches, across education, health and nutrition, and agriculture domains in Ghana.

### Country context

Ghana is a lower-middle income country with a population of 25 million people, over 40 % of whom are under 15 years of age [3]. Despite the high rates of economic growth occurred in the past two decades, Ghana is ranked 138th in the 2014 Human Development Index table, with a life expectancy at birth of 61 years, 7 mean years of schooling for adults and a Gross National Income (GDP) based on per capita purchasing power parity (PPP) of US$3532 [4]. The domestic economy is centred on subsistence farming, which accounts for nearly 40 % of the GDP and employs over 50 % of the workforce [5]. Around 25 % of the country’s population live in poverty based on the national-level poverty line, with this percentage increasing to 38 % in rural areas in contrast to 10 % in urban ones [6]. Food security in the marginal agricultural and arid areas varies with the seasons. The peak hunger seasons for the south of Ghana are from May to August whereas the north of Ghana experiences peak hunger seasons between July and October. The incidence of malnutrition in Ghana has been assessed through the Ghana Demographic and Health Surveys (GDHS) conducted every 5 years since 1988. From 1993 to 2008 there was some progress in reducing the rate of chronic malnutrition, with rates of stunting decreasing from 34 % to 29 % [6]. According to the 2003 and 2008 GDHS the prevalence of anaemia among children of 6–59 months of age increased marginally from 76 % in 2003 to 78 % in 2008. In 2008, the prevalence of anaemia among rural children aged under 5 years (84 %) was higher than in urban areas (68 %). The overall prevalence of stunting among school-aged children was 17 %, ranging from 13 % in the forest-savannah transitional zone to 21 % in the northern savannah [6]. The same study estimated that the prevalence of anaemia among school-aged children was 39 %. This, however, varied widely across ecological zones. Anaemia rates were highest in the northern savannah (65 %) and the coastal savannah zones (59 %) and least prevalent in the transitional zone (16 %).

### Complex intervention

This evaluation focusses on the Government of Ghana school feeding programme. As of 2011, the Ghana School Feeding Programme (GSFP) reached over 1.6 million primary school children in all 170 districts of Ghana. The programme is directly funded by the Government of Ghana, with a 4-year programme budget of over US$200 million. The GSFP was piloted in 10 schools in late 2005. By the end of 2009, GSFP had progressively grown to serve 1695 public schools with 656,624 pupils across the country. The GSFP is a complex intervention and was designed as a strategy to increase domestic food production, household incomes and food security in deprived communities [7]. The objectives of the strategy combined child-level education and nutrition, alongside household food production. GSFP co-ordination and implementation are undertaken by a national secretariat, with programme oversight provided by the Ministry of Local Government and Rural Development (MoLGRD). Line ministries offer technical support through the programme steering committee, although a number of NGOs and bilateral agencies are also involved with that support. The GSFP service delivery is provided through private caterers who are awarded contracts by the GSFP to procure, prepare and serve food to pupils in the targeted schools. Each caterer is responsible for procuring food items from the market, preparing school meals and distributing food to pupils. Cash transfers are made from the district assemblies, under the supervision of the District Implementation Committees (DICs), to caterers based on 40 Ghana pesewas (circa US$0.33) per child per day. Caterers are not permitted to serve more than three schools each, and profit is derived from savings made after food has been procured, prepared and distributed. Supervision at the school level is by the School Implementation Committee (SIC) and funds are intended to be released to caterers every 2 weeks. Storage is the responsibility of caterers and no rigid tendering process is enforced. The caterers are not restricted or guided in their procurement and are able to procure on a competitive basis without commitment to purchasing from small-scale farmers. The GSFP project document prioritises procurement from the community surrounding the assisted schools, broadening the focus to the district and national levels when food items are not available.

A recent supply chain analysis describes how caterer procurement decisions depend on costs (of food, transport, preparation) and on cash availability [8]. According to this study, the way and the extent to which caterers store food varies from district to district, but most have access to storage facilities (small household storage, school storage, or private storage). Caterers generally hire cooks to prepare food for students either in their homes or at school facilities. The main challenges faced by caterers include managing changes in food prices, hampered by the inability to mitigate price fluctuations due to delays in payments from the GSFP. Caterers reported that seasonal price variations between harvest and lean periods included price increases of up to 400 % [8]. The GSFP payments are received after the meals are served, resulting in caterers not having the resources to buy in bulk and guarantee a better and stable price to smallholder producers. Caterers were also reported to buy on credit from traders known as ‘market queens’ in Ghana, weakening their overall negotiation position. In addition, caterers also reported that payments often do not reflect the real number of pupils since enrolment often increases during the school term, which could possibly lead to either less food being served per child or higher costs faced by the caterers [9]. In practice, caterers often adapt to these challenges by reducing the quantity of food provided or by adjusting the quality of the food and adapting the menus. According to the supply chain study, procurement of food from smallholder farmers could help to mitigate the price volatility challenge. The study found that caterers were willing to procure their food from local farmers and that by buying from farmers, caterers could benefit from lower and more stable prices than those offered by traders on the market. Nonetheless, the reality is that almost all the food is still bought from markets [8].

